## Abstract

**Background:**

Laparoscopic Roux-en-Y gastric bypass (LRYGB) is considered the gold standard in bariatric surgery, achieving durable long-term weight loss with improvement of obesity-related comorbidities. Lately, the laparoscopic mini gastric bypass (LMGB) has gained worldwide popularity with similar results to LRYGB in terms of weight loss and comorbidity resolution. However, there is a lack of randomized controlled trials (RCT) comparing LMGB and LRYGB. This article describes the design and protocol of a randomized controlled trial comparing the outcomes of these two bariatric procedures.

**Methods/Design:**

The trial is designed as a single center, randomized, patient and observer blinded trial. The relevant ethics committee has approved the trial protocol. To demonstrate that LMGB is not inferior to LRYGB in terms of excess weight loss (EWL) the study is conducted as a non-inferiority trial with the sample-size calculations performed accordingly. EWL 12 months after surgery is the primary endpoint, whereas 3-year EWL, morbidity, mortality, remission of obesity related comorbidities, quality of life (QOL) and hormonal and lipid profile changes are secondary endpoints. Eighty patients, 18 years or older and with a body mass index (BMI) between 35 and 50 kg/m^2^ who meet the Swiss guidelines for the surgical treatment of morbid obesity will be randomized. The endpoints and baseline measurements will be assessed pre-surgery, peri-surgery and post-surgery (fixed follow up measurements are at discharge and at the time points 6 weeks and 12 and 36 months postoperatively).

**Discussion:**

With its 3-year follow up time, this RCT will provide important data on the impact of LMGB and LRYGB on EWL, remission of comorbidities, QOL and hormonal and lipid profile changes.

**Trial registration:**

ClinicalTrials.gov, NCT02601092. Registered on 28 September 2015.

**Electronic supplementary material:**

The online version of this article (doi:10.1186/s13063-017-1957-9) contains supplementary material, which is available to authorized users.

## Background

The globally growing incidence of obesity and its related comorbidities is one of the most challenging public health issues [1]. Morbid obesity reduces life expectancy, in particular among younger adults [2]. Bariatric surgery, the only effective treatment for morbidly obese patients, has shown effective long-term weight loss and significant reduction of obesity-related comorbidities and mortality in randomized controlled trials (RCT) [3–5]. The laparoscopic Roux-en-Y gastric bypass (LRYGB) is considered the gold standard among the different bariatric procedures, achieves durable long-term weight loss and improves obesity-related comorbidities [6, 7]. The laparoscopic mini gastric bypass (LMGB), first reported by Rutledge et al. [8], has recently gained popularity as a new procedure for the treatment of morbid obesity. LMGB is suggested to be a technically less demanding operation compared to LRYGB and offers comparable benefits. Several studies have been published assessing the efficacy and safety of LMGB. The first and only randomized controlled trial comparing the LRYGB to LMGB was carried out by Lee et al. in 2005 [9]. The authors observed excess weight loss (EWL) of 64.9% after LMGB and of 64.4% after one and two years, respectively. In comparison, patients with LRYGB had EWL of 58.7% and 60.0%, respectively. Excess weight (EW) is defined as the amount of weight that is in excess of the ideal body weight (IBW), which is determined as a body mass index (BMI) of 25 kg/m^2^. Therefore, EWL is the quotient of weight loss and EW. In addition, LMGB patients had fewer postoperative complications and shorter hospitalization.

Given the increasing number of bariatric procedures performed worldwide [10], the impact on weight loss, morbidity and mortality of LMGB in comparison to LRYGB needs to be further assessed in randomized controlled trials. Therefore, the aim of the current trial is to analyze the EWL and resolution of comorbidities with LMGB and LRYGB. Furthermore, the differences in hormone levels and changes in the lipid status of patients undergoing one of these two operations will be analyzed. These results have the potential to influence bariatric surgery guidelines profoundly and may bring additional insights in the pathophysiology of the intestinal tract after bariatric surgery.

## Methods/Design

### Primary objective

The general objective of this study is to compare LMGB to LRYGB in terms of clinical outcome and safety parameters. The primary objective of the study is to evaluate the non-inferiority of LMGB in comparison to LRYGB in terms of EWL (percent) one year after surgery.

### Secondary objective

The secondary objectives are the long-term effects of LMGB on weight loss, the perioperative and postoperative morbidity and the changes in different pathophysiological parameters during the study period: EWL at 36 months, morbidity, mortality, operative time, length of stay, subjective perception of appetite and satiety, quality of life (QOL), incidence of dumping syndrome, hormone levels (ghrelin, glucagon-like peptide 1, peptide YY, insulin), bile acids and lipid profile and functionality.

### Study design and site

This single center, randomized, controlled, patient and observer blinded, non-inferiority trial is being conducted at the Limmattal Hospital in Zurich-Schlieren, a reference center for bariatric surgery according to the Swiss Study Group for Morbid Obesity (SMOB). The trial has been registered on ClinicalTrials.gov under the identifier NCT02601092. This protocol has been written in accordance with the Standard Protocol Items: Recommendations for Interventional Trials (SPIRIT) guidelines (Additional file 1). A figure showing the planned visit and examination schedule is presented in Fig. 1.

**Fig. 1 Fig1:**
[figure not shown]
Schedule of enrollment, interventions, and assessments according to the Standard Protocol Items: Recommendations for Interventional Trials (SPIRIT) guideline. *LRYGB* laparoscopic Roux-en-Y gastric bypass, *LMGB* laparoscopic mini gastric bypass, *GERD* gastroesophageal reflux disease, *QOL* quality of life

### Sample size

A total of 80 patients will be randomized, with 40 patients assigned to each treatment arm. A loss of follow up at one year of 2.5% is considered realistic and it has been calculated to account for a dropout rate of 10%.

### Inclusion criteria

Patients aged 18 years or older with a BMI between 35 and 50 kg/m^2^ and eligible for bariatric surgery according to the SMOB guidelines will be enrolled.

### Exclusion criteria

Patients will be excluded on the following basis:Missing informed consentLack of conservative weight loss treatment over 2 yearsMalignancyInflammatory bowel diseaseExpected lack of compliance after multidisciplinary evaluation for surgeryPregnancyBMI over 50 kg/m^2^

Preoperatively, patients will be assessed by a nutritionist, endocrinologist, psychiatrist and general surgeon. If more than three appointments are not attended or if there are any contraindications due to severe psychiatric comorbidities, the operation will be postponed or cancelled.

### Randomization

Eligible patients, who give confirmed consent, are randomly assigned to one of the two operating techniques. Randomization will be performed using sequentially numbered, sealed, opaque envelopes. Computer-generated block randomization is used to ensure an equal number of patients in each treatment group. The block size used is not available from the study protocol and is unknown to the investigator, to keep the potential for selection bias at the lowest level possible. Patients will be allocated to a study group by the operating surgeon immediately prior to the operation.

### Interventions

Patients will receive standard preoperative assessment including endocrine, pulmonary function and cardiovascular assessment, psychological assessment, gastroscopy with *Helicobacter pylori* testing and abdominal ultrasound to check for liver size and gallstones. The operation will always be performed by the same surgeon with experience of performing over 1000 bariatric procedures. Blinded preoperative and postoperative follow up will be independently performed by two study physicians. The study design flow diagram is presented in Fig. 2.

**Fig. 2 Fig2:**
[figure not shown]
Flow diagram of the study design. *LMGB* laparoscopic mini gastric bypass, *LRYGB* laparoscopic Roux-en-Y gastric bypass, *BMI* body mass index

### Laparoscopic Roux-en-Y gastric bypass (LRYGB)

After gastroesophageal junction identification, the stomach is transected with a linear stapler entering the lesser sac 3–5 cm below the junction, creating a small gastric pouch with a volume of approximately 30 ml. A 60-cm biliopancreatic limb is measured and an antecolic end-to-side gastroenterostomy is formed using a 25-mm circular stapler. A stapled side-to-side jejunojejunostomy is formed 150 cm distally (Fig. 3). Intermesenteric and Petersen spaces are closed with non-absorbable sutures. All patients will be discharged on daily multivitamin and calcium tablets. Vitamin levels will be assessed during follow up and supplementation undertaken if required.

**Fig. 3 Fig3:**
[figure not shown]
Laparoscopic Roux-en-Y gastric bypass. The alimentary limb is 150 cm in *length* and is in the antecolic position. The mesentery defect is closed with interrupted sutures

### Laparoscopic mini gastric bypass (LMGB)

Stapled division of the stomach at the junction of the body and antrum is undertaken, at a location where a jejunal loop can be comfortably brought up (Fig. 4). A 36 French bougie is passed by the anesthetist and held against the lesser curvature. A very long gastric pouch is created by resection of the stomach parallel to the lesser curvature towards the angle of His. No short gastric vessels are divided. The bypassed stomach lies on the patients left, and the narrow lesser-curvature gastric pouch lies on the patient’s midline to the right of the bypassed stomach. A point is selected on the small bowel 200 cm distal to the ligament of Treitz. The jejunal loop is brought up lying antecolic, and a linear stapler (60 mm) is used to join the stomach and the small bowel at this point. The linear stapler enterotomy site is then closed with a running suture. The greater omentum is tucked between the gastric tube and the bypassed stomach [8]. Finally, Petersen’s space is closed with a non-absorbable suture. All patients will be discharged with daily oral multivitamins and calcium tablets. Vitamin levels will be assessed regularly during follow up and supplementation undertaken if required.

**Fig. 4 Fig4:**
[figure not shown]
Laparoscopic mini gastric bypass. The *narrow* gastric tube is the *diameter* of a 36 French bougie. The gastroenterostomy is created at the small bowel 200 cm distal to the Trietz ligament

### Study visits

Physicians and study nurses blinded to the intervention will perform study documentation and patient assessment. Since the trial is designed as an observer and patient blinded RCT, information about the surgical procedure will not be disclosed to any assessors during the follow up examinations. There will be five study visits in total. The first visit will be preoperative after informed consent is obtained. Postoperatively, study visits will be performed at discharge, 6 weeks and 12 and 36 months. Each study visit includes collection of data on weight, blood tests, in particular, metabolic parameters such as hormonal assessment, glucose levels and lipid profile. Measurement of metabolic parameters will be conducted preoperatively and 6 weeks and 12 and 36 months postoperatively after a 12-hour fast and at 60 and 120 minutes after a standardized test meal (375 kcal). In addition, questionnaires will be also assessed (Gastrointestinal Quality of Life Index (GIQLI), Simplified Nutritional Appetite Questionnaire (SNAQ), Gastroesophageal Reflux Disease Questionnaire (GERDQ), Bariatric Analysis And Reporting Outcome System (BAROS) and the Sigstad score) at each visit. Furthermore, triglycerides (TG), total cholesterol, high-density lipoprotein (HDL), low-density lipoprotein (LDL), ghrelin, glucagon-like peptide-1 (GLP-1), peptide YY (PYY), glucose, insulin and bile acids will also be evaluated. Postoperatively additional data on morbidity (surgical and non-surgical short-term and long-term complications) and mortality will be collected.

### Study endpoints

#### Primary endpoint

The primary endpoint is the EWL at 12 months after surgery (LRYGB or LMGB). For the EWL calculation (percent) the pre-surgical total body weight (at the patient’s hospital entry time) and postsurgical total body weight at one year postoperative is measured.

#### Secondary endpoints

Long-term EWL at 36 months after surgery (in percent)Early surgical and non-surgical complications (≤30 days) according to the Clavien-Dindo classification [11]Operation timeLength of hospital stayHormonal levels (ghrelin, GLP-1, PYY, glucose and insulin)Lipid profileBile acidsIncidence of GERDSatiety degreeDumpingQuality of life questionnaires

Levels of glucose, insulin and HbA1c will be determined for assessment of glucose homeostasis. TG, total cholesterol, LDL cholesterol (LDL-C), HDL cholesterol (HDL-C) and HDL/LDL cholesterol quotients will be measured to create a lipid profile. Quality of life, satiety degree, incidence of reflux and dumping will be investigated by questionnaires (GIQLI [12], SNAQ [13], GERDQ [14], BAROS [15] and the Sigstad score [16]). Secondary endpoints will be evaluated preoperatively, at discharge, 6 weeks and 12 and 36 months postoperatively.

### Blinding

With the exception of the team in the operating theatre, all medical and non-medical practitioners and patients will be blinded to the procedure. The procedure will be named as *study bypass* in all medical records. Unblinding is permitted in the case of surgical or medical complications, emergency consultation or other ethical considerations.

### Statistical analyses

#### Sample size

If LMGB is non-inferior to LRYGB, 72 patients are required (36 patients per study arm) to have an 80% chance that the lower limit of the one-sided 97.5% confidence interval (equivalently a 95% two-sided confidence interval), does not include the non-inferiority limit of –10% EWL when assessed at 12 months. Given an anticipated dropout rate of 10%, the total number of patients to be included in the study is 80 (40 patients per arm). The non-inferiority limit of –10% EWL was chosen based on expert bariatric opinion. Furthermore a standard deviation of 15 was assumed in both arms according to a study from Lee et al. [9]. For further details on calculations see “Analysis of endpoints”.

#### Analysis of endpoints

The study results will be reported in adherence to the extension of the Consolidated Standards of Reporting Trials (CONSORT) statement from 2010 on reporting of non-inferiority randomized trials [17]. Summary statistics will be used to describe and compare patient characteristics of all suitable but non-included patients and all included patients (overall and stratified for the two treatment arms). Study endpoints will primarily be analyzed for the per protocol (PP) population. Sensitivity analysis will be conducted for the intention-to-treat (ITT) population. Thereby the ITT population includes all randomized patients in the groups to which they were randomly assigned, regardless of their adherence to the entry criteria, regardless of the treatment they actually received and regardless of subsequent withdrawal or deviation from the protocol. In the PP population all protocol violators, including anyone who switched groups or missed measurements are excluded. For each group, number of participants (denominator) included in each analysis and whether the analysis was by original assigned groups will be given. Additional sensitivity analysis will be used if, despite all efforts taken to ensure complete data collection, the number of missing data is non-negligible or could potentially bias the results and conclusions.

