#### Analysis of secondary endpoints

To investigate non-inferiority of the experimental treatment in the long term, analysis used for the primary endpoint will be repeated for EWL at 36 months post-surgery. All other endpoints will be analyzed under the assumption of superiority of the experimental treatment compared to the standard treatment. To compare the duration of surgery and the length of hospital stay between the two treatment groups, the Wilcoxon signed-rank test will be conducted (as we assume the data to be right-skewed).

The number of perioperative and postoperative complications will be analyzed by the chi-squared test or Fisher’s exact test, dependent on the observed numbers in a 2 × 2 contingency table. Additionally, we will compare the risk for complications in the two groups by calculating the risk difference with 95% confidence interval. The other secondary endpoints will be investigated using appropriate explorative methods and graphical visualization.

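### The per-protocol set leads for every endpoint, including the superiority comparisons of operation time, hospital stay and complications, where the as-randomised set should lead

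*Protocol article*

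**What the plan says.** The protocol article sets one rule for all endpoints under Analysis of endpoints: "Study endpoints will primarily be analyzed for the per protocol (PP) population". The other set has a supporting role: "Sensitivity analysis will be conducted for the intention-to-treat (ITT) population". ITT is properly defined there as everyone randomised, in the assigned arm, whatever happened afterwards. The per-protocol set is defined by exclusion: "In the PP population all protocol violators, including anyone who switched groups or missed measurements are excluded".

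Analysis of secondary endpoints repeats the non-inferiority analysis for EWL at 36 months and then says: "All other endpoints will be analyzed under the assumption of superiority of the experimental treatment compared to the standard treatment". Tests are named for three of these endpoints. Operation time and length of stay get a Wilcoxon test. For complications, "The number of perioperative and postoperative complications will be analyzed by the chi-squared test or Fisher’s exact test", depending on the observed counts, with a risk difference and 95% confidence interval. The remaining endpoints are to be explored descriptively and graphically. No sentence in these sections gives the superiority or complication endpoints a different analysis set.

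**The concern.** The usual reason for giving weight to a per-protocol analysis in a non-inferiority trial is that crossovers and deviations blur the contrast between arms under ITT, which can make an inferior treatment look non-inferior. That reason does not carry over to a superiority comparison. There, excluding patients after randomisation gives up the comparability that randomisation provided, and nothing is gained in caution.

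The exclusion reasons make this more than a formality. According to Randomization, the surgeon allocates the patient just before the operation, so a switch of procedure would mostly arise in theatre, plausibly because of operative difficulty. Such a patient may well have a long operation, a long stay or a complication. Missed measurements can follow from withdrawal or illness. Neither reason need be balanced between arms.

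At stake is the leading result for the three secondary comparisons with named tests, above all complications. The trial states that it will answer questions about the safety of LMGB.

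**Working it through.** **The plan's own figure.** Inputs from Sample size under Statistical analyses: margin 10 points of EWL ("The non-inferiority limit of –10% EWL was chosen based on expert bariatric opinion"), SD 15 ("Furthermore a standard deviation of 15 was assumed in both arms"), one-sided alpha 0.025 ("one-sided 97.5% confidence interval (equivalently a 95% two-sided confidence interval"), power 80%, and a true difference of 0.

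- n per arm = 2 × (1.960 + 0.842)² × 15² / 10² = 35.3, rounded up to 36, so 72 in total.
- 72 / (1 − 0.10) = 80 randomised, 40 per arm.

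Both stated figures reproduce. This point disputes neither, and the 36 per arm relates only to EWL.

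**The rule set against each kind of endpoint.**

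- EWL at 12 and 36 months: non-inferiority, per-protocol primary. This is conventional, with ITT alongside.
- Operation time, length of stay, complications: superiority, per-protocol primary. The reason for using per-protocol does not apply.
- These three endpoints are also observed early. Operation time is known at surgery, length of stay at discharge, and the listed complication endpoint covers the first 30 days. Missing later data is therefore no ground for dropping a patient from them. The exclusion rule, however, does not say that only a missed measurement of the endpoint in question counts.

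**Illustration for complications.** The document gives no complication or conversion rate, so all counts here are assumed. The number excluded is set at 4 of 40 per arm, which equals the 10% dropout allowance. Risk difference is LMGB minus LRYGB, and the per-protocol denominator is 40 − 4 = 36.

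| Complications, LMGB / LRYGB | Excluded LMGB patients with a complication (LRYGB: 0) | ITT difference | Per-protocol difference |
|---|---|---|---|
| 6 / 6 | 2 | 6/40 − 6/40 = 0 | 4/36 − 6/36 = −5.6 points |
| 6 / 6 | 4 | 0 | 2/36 − 6/36 = −11.1 points |
| 8 / 4 | 1 | 8/40 − 4/40 = +10.0 points | 7/36 − 4/36 = +8.3 points |
| 8 / 4 | 4 | +10.0 points | 4/36 − 4/36 = 0 |

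The effect can run the other way. With 4 LMGB and 8 LRYGB complications, ITT gives 4/40 − 8/40 = −10.0 points. If all 4 excluded LRYGB patients had a complication and no excluded LMGB patient did, per-protocol gives 4/36 − 4/36 = 0, and a real advantage of LMGB disappears.

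With only 1 exclusion per arm (2.5% of 40, the one-year loss that the first Sample size section calls realistic), 6 complications per arm, and the one excluded LMGB patient having a complication, the difference is 5/39 − 6/39 = −2.6 points. If excluded patients have complications at the same rate as retained ones in both arms, there is no expected bias.

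**The case against.** The strongest reply has four parts.

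- **ITT will be reported.** It is fully defined, denominators are promised for each analysis, reporting follows the CONSORT extension for non-inferiority trials, and further sensitivity analyses are planned if missing data could bias the results. A disagreement between the sets would be visible. This stands as mitigation, but the result designated as leading would still be the per-protocol one.
- **The scope is narrow.** Only three secondary endpoints other than EWL have named tests, none of them the basis of the sample size, and the rest are exploratory. This stands, and it lowers the severity.
- **Exclusions may be few.** One surgeon with more than 1000 bariatric procedures operates, allocation comes just before surgery, and little loss is expected. This is reasonable, but the definition also removes all other protocol violators, and their number cannot be predicted from the text.
- **Details by endpoint belong in the full protocol or SAP.** The absence of a separate safety set from an article is no fault. The criticism is of a rule that the article does state, without limiting it to EWL.

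A reader might go further and infer that per-protocol mortality must be zero in both arms, because a patient who dies misses measurements. The text does not establish that. It never says that death counts as a protocol violation, and since denominators are given per analysis, exclusion may be meant endpoint by endpoint. Nor is mortality in the list under Secondary endpoints or among the named tests, although it appears in the Abstract, Secondary objective and Study visits. Likewise, a complication is not in itself a reason for exclusion. That the set removes patients who had trouble is a plausible mechanism, not something the rule states.

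**Conclusion.** The concern holds at moderate severity. As written, per-protocol leads for endpoints analysed for superiority, and no other sentence corrects this. Exclusions after randomisation can then distort the comparisons of operation time, length of stay and complications. On a literal reading, a recorded early complication can drop out because of a later missed visit; whether that was intended is unclear.

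The document does not fix the size or direction of the distortion. In the illustrations it runs from 1.7 points (10.0 − 8.3) to 11.1 points of risk difference. These rest on assumed complication counts, on 1 or 4 exclusions per arm, and on the excluded patients with complications all falling in one arm. They show what can happen at the plan's own loss and dropout rates and are not forecasts.

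It does not follow that the main conclusion is compromised. Per-protocol is a conventional set for the EWL non-inferiority analyses, and the primary endpoint is not affected by this point.

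**What to change.** Under Analysis of endpoints, replace the general rule with rules by type of endpoint:

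- Per-protocol is a primary set only for the non-inferiority analyses of EWL at 12 and 36 months.
- ITT, as randomised, is primary for all endpoints analysed for superiority, with per-protocol as sensitivity.
- Complications and deaths are reported in all operated patients by randomised arm, with a supportive tabulation by operation received and per-protocol as sensitivity.

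It would also help to say whether a missed measurement excludes a patient only from the endpoint concerned.

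The cost is a few sentences. Both sets are already defined and both analyses already planned, so mainly their roles change. The sample size stays at 72 evaluable and 80 randomised, and no additional data are needed. The article reports enrolment as still open, so if the plan has not already settled this, the change should be documented before outcome data are examined by arm.

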#### Analysis of primary endpoint

The primary endpoint is the EWL at 12 months post-surgery. To examine non-inferiority of the experimental compared to standard treatment, we assess if the two-sided confidence interval of the difference between the mean EWL in the experimental treatment group and the mean EWL in the standard treatment group does not include the non-inferiority limit of –10% EWL.

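### Non-inferiority rests on the per-protocol set alone: the criterion should also require the ITT interval to clear –10 EWL points

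*Protocol article*

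**What the plan says.** Three statements in the protocol article fix the rule.

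- *Analysis of endpoints* sets the ranking of the populations: "Study endpoints will primarily be analyzed for the per protocol (PP) population", followed by "Sensitivity analysis will be conducted for the intention-to-treat (ITT) population".
- The same section defines the sets. For PP: "In the PP population all protocol violators, including anyone who switched groups or missed measurements are excluded". For ITT: "the ITT population includes all randomized patients in the groups to which they were randomly assigned", whatever treatment was received and whether or not the patient later withdrew.
- *Analysis of primary endpoint* gives the criterion: the two-sided interval for the LMGB minus LRYGB difference in mean EWL "does not include the non-inferiority limit of –10% EWL". It names no population and says nothing about agreement between them.

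The article also commits to the CONSORT extension for non-inferiority trials, to reporting the denominator of each analysis, and to further sensitivity analyses if missing data are more than negligible. None of these makes the conclusion depend on the ITT result.

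**The concern.** Read together, these sections mean that a PP interval lying above –10 meets the primary criterion, and an ITT interval that reaches –10 has no stated consequence.

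Group switches and missed measurements arise after randomisation, and the two operations differ, so the reasons for exclusion could differ by arm. If the patients removed from the LMGB arm did worse than those kept, the PP comparison flatters LMGB and the intended one-sided 2.5% error no longer holds for the randomised comparison.

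The wording on missed measurements widens the opening. *Study visits* lists five visits with weight, blood tests and several questionnaires, with metabolic tests around a test meal at four of the time points. Taken literally, a patient with a valid 12-month weight could leave the primary analysis for missing something unrelated to it.

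**Working it through.** **Inputs from the article** (*Statistical analyses, Sample size*): margin –10 EWL points, SD 15 in both arms, one-sided 2.5% error (95% two-sided interval), 80% power, 36 evaluable patients per arm, 10% dropout, 40 per arm randomised. The true difference for the power calculation is not given as a number; 0 is assumed because it reproduces the stated size.

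**The plan's own figure.** n per arm = 2 × 15² × (1.96 + 0.84)² / 10² ≈ 35.3, rounded up to 36, so 72 in total; 72 / 0.90 = 80. This agrees with the article. The point concerns the decision rule, not the sample size.

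**How close the verdict can be.** With SD 15 the t-based half-width of the interval is 7.05 at 36 per arm and 6.68 at 40 per arm. The trial passes if the observed difference is above –10 + 7.05 = –2.95, or –10 + 6.68 = –3.32. A shift of a few points can therefore change the verdict.

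**Effect of unequal exclusion.** Suppose k of 40 LMGB patients leave PP, their mean EWL is d points below that of the LMGB patients who stay, and nobody leaves the LRYGB arm.

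- Shift of the PP difference relative to the randomised difference = k × d / 40.
- SE of the PP difference = 15 × √(1/(40 – k) + 1/40).
- Chance that PP passes when the randomised difference is exactly –10 ≈ 1 – Φ(1.96 – shift/SE).

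For k = 4 and d = 30: shift = 4 × 30 / 40 = 3.0; SE = 15 × √(1/36 + 1/40) = 3.45; 1 – Φ(1.96 – 0.87) = 1 – Φ(1.09) = 13.8%. With the planned SE of 15 × √(2/36) = 3.54 it is 1 – Φ(1.11) = 13.3%.

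The last three columns come from a simulation (50,000 runs per row, t-based 95% intervals, all 12-month weights available for ITT):

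| LMGB excluded (k) | Deficit (d) | Shift | Formula | PP passes | ITT passes | PP passes, ITT fails |
|---|---|---|---|---|---|---|
| 4 | 0 | 0 | 2.5% | 2.4% | 2.5% | 0.5% |
| 2 | 15 | 0.75 | 4.1% | 3.9% | 2.4% | 1.6% |
| 4 | 15 | 1.50 | 6.4% | 6.1% | 2.2% | 4.0% |
| 2 | 30 | 1.50 | 6.4% | 6.2% | 1.9% | 4.3% |
| 4 | 30 | 3.00 | 13.8% | 13.8% | 1.6% | 12.2% |

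Four of 40 equals the article's 10% dropout allowance applied to one arm. The values of k and d, and the absence of LRYGB exclusions, are assumptions.

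**Cost of requiring both sets.** At a true difference of 0, with four LMGB patients excluded at random and complete ITT weights, simulated power is 81% for PP alone, 83% for ITT alone and 80% for both together. If the four excluded patients are 15 or 30 points lower while the randomised difference is 0, joint power is 83% or 79%, close to that of ITT alone.

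**The case against.** A reader might infer that making PP primary is itself an error. The article does not support that. ITT counts a patient who switched procedure in the arm they left, which pulls the arms together and can favour a non-inferiority claim, so PP-primary is an accepted choice. The weakness is only that agreement is not required.

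A reader might also infer that a contradictory ITT result would be ignored. The article does not say so. ITT is prespecified, defined and would be reported with its denominator, so disagreement would be visible. Its interpretation may be set out in an analysis plan that is not shown. What stands is that the article itself ranks the populations and states the criterion, and under that text a PP pass is sufficient.

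It is tempting to list complications among the reasons for exclusion, since they offer an obvious route to poor weight loss. The article names protocol violators, switchers and missed measurements; complications are a secondary endpoint, not a stated exclusion.

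Finally, 13% to 14% should not be read as the expected error rate. It needs four exclusions in one arm, none in the other, and a deficit of 2 SD. With four LMGB and two LRYGB exclusions at the same 30-point deficit, the net shift is 3.0 – 1.5 = 1.5 points and the error about 6%. Equal exclusions with equal deficits give no shift, and exclusions concentrated in LRYGB would work against LMGB. Allocation immediately before surgery, a single surgeon and patient blinding make preference-driven switching unlikely. The article regards 2.5% loss at one year as realistic, which is 0.025 × 80 = 2 patients. A patient with no 12-month weight adds no observed outcome to ITT either, so the both-sets rule does not by itself repair that loss.

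**Conclusion.** The point holds in a limited form. As written, PP alone decides the primary claim, and it offers no safeguard if exclusions are related to outcome and unbalanced between arms. At a true randomised difference of –10, the false-claim rate in the scenarios examined runs from about 2.4%, when exclusion is unrelated to outcome, through 3.9% to 6.1% for a 15-point deficit, to 13% to 14% at the extreme. The range depends entirely on assumed numbers and deficits in one arm, and on complete 12-month weights for ITT. The stated sample size is not in question. Because the remedy uses two analyses already planned, this is a cheap improvement and not a flaw that invalidates the design.

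**What to change.** In *Analysis of endpoints* and *Analysis of primary endpoint*:

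1. State that non-inferiority is concluded only if the lower limit of the two-sided 95% confidence interval for LMGB minus LRYGB lies above –10 EWL points in both the PP and the ITT population, and is not claimed if the two disagree.
2. For the primary endpoint, limit the missed-measurement exclusion to a missing 12-month weight.
3. State that the 12-month weight of patients who switched procedure is included in ITT, in the arm to which they were randomised.

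The cost is a few sentences and a small loss of power: about 80% jointly against 81% for PP alone, under four random LMGB exclusions and complete ITT weights. No increase in the 80 patients is needed.
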